## Abstract

**Introduction:**

Uveal melanoma (UM) is a rare ocular cancer. While germline mutations in genes such as BAP1 and MBD4 account for approximately 20% of familial UM cases, the hereditary factors underlying the remaining cases remain unknown. Epidemiological studies have suggested an increased risk of prostate cancer, thyroid cancer, and leukemia among patients with UM, indicating potential unidentified genetic predispositions. This study aims to identify new candidate genes associated with a hereditary predisposition to UM.

**Methods:**

This single-center study, conducted at Centre Jean Perrin, will involve the exome sequencing of 50 patients with UM who do not harbor known pathogenic variants in the BAP1 or MBD4 genes. The primary objective is to identify novel candidate genes associated with hereditary cancer predisposition among UM patients. A several-step-bioinformatic analysis will be conducted to identify the genes of interest. A secondary objective is to explore genes known to be involved in predisposition to other cancers, already described in the occurrence of uveal melanoma, but where an association has not been fully established yet. The study has begun in October 2024, with patient recruitment lasting 12 months. No follow-up period is planned, but the duration of the genetic analyses is estimated at six months, with the final study report expected by October 2026.

**Discussion:**

The identification of novel hereditary predisposition genes for UM could significantly enhance genetic counselling and surveillance strategies for families affected. This study could also contribute to a better understanding of the genetic landscape of UM, potentially leading to more personalized and effective options for its detection.

**Trial registration:**

ClinicalTrials.gov, identifier NCT06550674, registered in August 2024. Protocol: version 1.0, January 18^th^, 2024.

## Introduction

1

Uveal melanoma (UM) is a rare, aggressive ocular cancer occurring in adults, with an incidence of 1 to 9 cases per million people per year (1). It arises from melanocytes in the uveal tract, which includes the choroid, the ciliary body, and the iris. The most common symptoms are blurred or distorted vision, visual field loss or photopsia (2, 3). The 5-year survival rates are quite encouraging for localized and regional stages, standing at 85% and 67% respectively. However, the most significant challenge in managing this disease occurs in the metastatic stage, where the survival rate drops to 16% (4). With more than 30% of these patients developing metastases, almost invariably in the liver, UM is therefore known for its poor prognosis as a result of the absence of efficacious treatments, with a median survival of only 10 months (5–7).

The identification of candidate genes for hereditary predisposition to uveal melanoma is of great interest, as it holds the potential to revolutionize patient care. Indeed, validation of these potential genes could enable their integration into a diagnostic approach. Patients could then be offered screening and preventive measures tailored to their tumor spectrum, as well as appropriate familial genetic counselling. Following this line of research, our study, IGCMU (*Identification de nouveaux Gènes Candidats à la predisposition héréditaire au Mélanome de l’Uvée*) aims to identify new candidate genes for hereditary predisposition to UM, particularly in cases not linked to BAP1 or MBD4. We will also explore the role of genes associated with other hereditary cancer syndromes and examine their potential involvement in UM, contributing to a broader understanding of the genetic landscape of this rare cancer.

## Methods and analysis

2

### Study design

2.1

This is a single-center interventional study on the genetic constitutional analysis of UM patients. The intervention involves blood and mouth swabs collection for genetic analysis, coupled with consultation with oncologists-geneticists.

### Coordination

2.2

Centre Jean PERRIN (Clermont-Ferrand, France) is the sponsor of the study. The clinical research department is responsible for trial management (regulatory and financial aspects) and data management. All the data analyses will be conducted in the oncology-genetics department.

### Objectives and outcomes

2.3

#### Primary objective and outcome measure

2.3.1

The main objective is to identify new candidate genes for hereditary cancer predisposition among patients with uveal melanoma. The variants of interest will be selected from the data using the following filters: variants with a frequency <1% (GnomAD), if at least 2 affect the same gene; truncating or missense from a list of cancer genes; and a combined annotation-dependent depletion (CADD) score > 20 (COSMIC Tier1 and Tier2). The variants will then be interpreted using various databases and prediction tools.

#### Secondary objective and outcome measure

2.3.2

The secondary objective is to explore genes known to be involved in predisposition to other cancers already described in relation to the occurrence of uveal melanoma, but for which the association has not yet been established with certainty.

The outcome of this objective will be measured from the number of patients with a mutation on the BRCA1, BRCA2, CHEK2, PALB2, POT1, MSH6, MLH1, SMARCE1, TP53AIP1, MLH2 and PMS2 genes.

### Setting and eligibility criteria

2.4

Patients will be eligible to participate in the study if they meet the following selection criteria:

The inclusion criteria will be:

Age ≥ 18 yearsPatients with a personal history of uveal melanoma (newly diagnosed, undergoing treatment, or in follow-up)Affiliation to the social security system or qualifying for cover by the system

The exclusion criteria will be:

Pathogenic causal variant identified in BAP1 or MBD4Patients not consenting to constitutional genetic analysis for diagnostic purposesPatients not consenting to constitutional genetic analysis for research purposesPregnant or breastfeeding womenPatients under guardianship or curatorship

To participate in the IGCMU study, patients meeting the selection criteria will be invited in two distinct ways: either by a participating clinician who is managing their uveal melanoma, or by the French national association of patients with eye cancers (A.N.P.A.C.O.), who will present the study to its members via a presentation letter.

Individuals interested can directly contact the principal study investigator by email to apply for inclusion, or by calling the Centre Jean PERRIN oncology-genetics department. For each patient interested, a consultation with an oncologist-geneticist from the Centre Jean PERRIN oncology-genetics department will take place.

### Intervention and participant timeline

2.5

The study will follow a structured approach divided into two main phases: a recruitment phase and a genetic-analysis phase.

During the recruitment phase, patients diagnosed with UM and their family members (if applicable) will be approached for inclusion. Recruitment will take place over a period of 12 months. The geneticists and oncologists involved in the study will manage patient inclusions and organize sample collection with the help of the clinical research department.

Once consent is obtained, two types of biological samples will be collected from each participant: a blood sample (EDTA tube) and a mouth swab (FTA card). These samples will be taken either at Centre Jean PERRIN by clinical nurses or, if necessary, at the patient’s home by a private nurse. In the latter case, pre-paid envelopes will be provided to facilitate the shipment of the samples to the Centre’s molecular oncology-genetics laboratory.

During the genetic-analysis phase, the samples collected will undergo DNA extraction, library preparation, capture, and sequencing using the NextSeq Illumina platform.

Additionally, an enrichment analysis will be performed to determine whether any variants identified are associated with specific molecular pathways. Bioinformatics analyses will be performed by a dedicated bioinformatics technician attached to the study.

The expected total duration of the study is 18 months. After the first consultation, a second consultation can be arranged if necessary for further discussions of results.

### Whole exome sequencing

2.6

Germline DNA will be extracted from peripheral blood. Kapa library preparation kit and HyperExome probes (Roche) will be used for library preparation and capture. Sequencing will be performed on a NextSeq 2000 instrument (Illumina). All steps will be performed following the manufacturer’s guidelines.

### Bio-informatic analysis

2.7

De-multiplexing will be performed using BCLConvert Software (Illumina). Alignment will be performed on GRCh38 human genome reference using Burrows-Wheeler Aligner. Genome Analysis Toolkit (GATK), PICARD and Samtools tools will be used for base quality score recalibration and duplicate marking. Variant calling will be performed using two different tools GATK HaplotypeCaller and FreeBayes. Annotations will be performed using Ensembl VariantEffectPredictor and Annovar. Variants will be filtered for quality score ≥30, depth ≥ 30x, and present in ≥ 20% of reads.

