### Biological filters

2.8

For BAP1, MBD4 and all candidate gene of uveal melanoma, all variants whose frequency in the general population is < 1% will be analyzed. Variants will be classified according to the American College of Medical Genetics (ACMG) recommendations. In addition, if a BAP1 or MBD4 variant is identified in patients who have never had a genetic analysis, the result will be confirmed on the saliva sample and a consultation will be organized to report the results.

For all the others genes, the variants of interest will be selected from the data using the following filters: variants with a frequency <1% (GnomAD), if at least 2 affect the same gene; truncating; splice variant with a SPIP and SpliceAI predicted effect or missense with a combined annotation-dependent depletion (CADD) score > 20 from a list of cancer genes (COSMIC Tier1 and Tier2).

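### Blood-derived calls kept from 20% of reads are not checked for being inherited in the outcome genes, although a mouth swab is taken from every participant

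*Protocol article*

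**What the plan says.** All references are to the protocol article.

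- **Tissue sequenced (section 2.6):** "Germline DNA will be extracted from peripheral blood".
- **Call filter (section 2.7):** "Variants will be filtered for quality score ≥30, depth ≥ 30x, and present in ≥ 20% of reads". No check of allele balance is stated.
- **Samples taken (section 2.5):** "two types of biological samples will be collected from each participant: a blood sample (EDTA tube) and a mouth swab (FTA card"). The same section then says that "the samples collected will undergo DNA extraction, library preparation, capture, and sequencing using the NextSeq Illumina platform", without naming the tissue.
- **Use of the second tissue (section 2.8):** the trigger is "if a BAP1 or MBD4 variant is identified in patients who have never had a genetic analysis"; the action is that "the result will be confirmed on the saliva sample".
- **Filter for all other genes (section 2.8):** "variants with a frequency <1% (GnomAD), if at least 2 affect the same gene; truncating; splice variant with a SPIP and SpliceAI predicted effect". A CADD value above 20 is the condition for missense changes, and the gene list is COSMIC Tier 1 and Tier 2.
- **Secondary outcome (section 2.3.2):** the number of patients with a mutation in any of 11 named genes. The two-variants-per-gene condition is not stated for this count.

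**The concern.** The study sets out to find genes for hereditary predisposition, so a variant should be shown, or at least be likely, to be present in the germline. Blood DNA also contains variants acquired by blood-cell clones. An inherited heterozygous variant is expected in about half of the reads, whereas an acquired one can appear at a lower fraction. A cut at 20% leaves a wide band in which both kinds are kept.

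The steps that follow address other questions. Population frequency tests rarity, and the two-variant rule tests recurrence. CADD, the splice predictors and ACMG classification bear on damage or pathogenicity. Tissue expression and pathway enrichment bear on plausibility. No segregation step is stated, although section 2.5 mentions approaching family members.

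The design has some exposure to this. The Introduction puts most diagnoses between 50 and 70 years, section 2.4 admits patients under treatment or in follow-up, and the main filter works on a cancer-gene list. The Introduction also cites excess leukemia among patients with uveal melanoma as a finding that BAP1 and MBD4 do not currently explain. A blood-cell variant mistaken for an inherited one could seem to support that idea.

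**Working it through.** The article gives no error rate, power or calculated sample size, so there is no figure to reproduce. The filter's behaviour follows from its own thresholds.

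**Inputs from the article:** minimum depth 30x, minimum read fraction 20%, about 50 patients (section 2.10, a recruitment estimate).

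**Assumptions, not in the article:** an inherited heterozygote has a true read fraction of 0.50 with no capture bias; an acquired clone has a true fraction between 0.10 and 0.30; between 0.5% and 5% of patients carry a passing clone in one given gene.

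**1. Chance that a clone passes the 20% cut.** With depth n and true fraction f, this is P(X ≥ 0.20n) for X ~ Binomial(n, f). The minimum is 6 of 30, 12 of 60 or 20 of 100 reads.

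| True fraction | 30x | 60x | 100x |
|---|---|---|---|
| 0.10 | 0.07 | 0.015 | 0.002 |
| 0.15 | 0.29 | 0.18 | 0.11 |
| 0.20 | 0.57 | 0.55 | 0.54 |
| 0.25 | 0.80 | 0.85 | 0.90 |
| 0.30 | 0.92 | 0.97 | 0.99 |

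More depth screens out clones below the cut but passes those above it more reliably.

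**2. True heterozygotes lost to the cut.** At 30x, P(X ≤ 5) for Binomial(30, 0.5) = 0.00016, or 0.02%.

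**3. Would a higher cut be enough?** At a 30% cut (9 of 30 reads), clones at 0.20 and 0.30 pass with probability 0.13 and 0.57, and 0.8% of heterozygotes are lost. A higher cut reduces the problem without removing it.

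**4. The two-variant rule.** If a share p of patients carry a clone *that passes* in one gene, then P(at least 2 of 50) = 1 − (1−p)^50 − 50p(1−p)^49.

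| p (assumed) | at least 1 of 50 | at least 2 of 50 |
|---|---|---|
| 0.5% | 0.22 | 0.03 |
| 1% | 0.39 | 0.09 |
| 2% | 0.64 | 0.26 |
| 5% | 0.92 | 0.72 |

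Here p must already include the chance of passing. If 1% or 2% of patients carry a clone at true fraction 0.20 read at 30x, the passing share is 0.57% or 1.14% (p × 0.5725), and the chance of at least two falls to 0.03 or 0.11.

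**5. What a flag would catch.** A flag at 20-35% of reads covers 6 to 10 reads at 30x.
- True heterozygotes flagged: 4.9% at 30x (P(6 ≤ X ≤ 10), Binomial(30, 0.5)), 1.4% at 60x and 0.2% at 100x.
- A clone at 0.30 has 11 or more of 30 reads with probability 0.27, so it can escape the flag. Nominated variants therefore need the swab check as well.
- A two-sided binomial test against 50% at p < 0.001 would flag nothing at 30x, because the lowest retained count, 6 of 30, gives p = 2 × 0.000715 = 0.0014.

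**The case against.** **The biology comes from outside the document.** The article does not say that acquired variants occur in these patients, at what read fraction, or in which genes. This stands: clone fraction and prevalence are assumptions, and the number of false candidates cannot be computed.

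**The filters are not the last word.** Section 2.9 has each variant of interest interpreted individually and selects on uveal expression. Section 2.8 requires two variants in the same gene. The product is a list of candidates, and the Introduction makes diagnostic use depend on validation. This also stands. A reader might infer that a recurrent acquired variant would be reported as hereditary; the text supports only that it could be nominated. A reader might likewise infer that the 11-gene count will be inflated. That is possible, since one patient is enough to change the count, but nothing in the article gives it a size.

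**Silence is not exclusion.** Section 2.8 does not say that the swab is used for nothing else, section 2.5 can be read as sequencing both samples, and a condensed article may leave laboratory confirmation to the full protocol. This stands in part. The tissue, the cut-off and the trigger for confirmation are all written out, section 2.6 names blood, and confirmation is tied to two genes that are not the ones being sought. The passages need reconciling in any case.

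**A 20% cut is a legitimate sensitivity choice.** Agreed. A reader might infer that the threshold itself is an error; it is not. The weakness lies in combining that cut with blood DNA and no stated inheritance check for the outcome genes.

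**Conclusion.** The point holds as a gap in the stated rules and should be closed before the analysis. As written, an acquired blood-cell variant in a COSMIC cancer gene could satisfy the primary filters, and one in any of the 11 named genes could be counted in the secondary outcome, with no stated step to reveal that it is not inherited.

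The pass probabilities in step 1 follow from the article's thresholds once a clone fraction is assumed. At fractions of 0.20 to 0.30 a clone passes more often than not at any depth examined; at 0.10 it rarely does. The chance of two carriers in one gene depends wholly on an assumed prevalence, and the width of its range, 0.03 to 0.72, shows how little the document pins it down. The two-variant rule lowers the risk for the primary outcome without excluding it.

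**What to change.** 1. Keep the 20% call threshold, and report the read fraction and depth of every variant of interest.
2. Flag each call at 20-35% of reads. Do not use a binomial test at p < 0.001 as the flag, for the reason in step 5 of the working.
3. Before a flagged variant, or any finally nominated variant, enters the primary or secondary outcome, confirm it in the stored mouth-swab DNA. Require a heterozygous level, near 50%, because swabs contain blood cells and mere presence would not separate the two origins.
4. Reconcile sections 2.5, 2.6 and 2.8 on which samples are sequenced and what the swab (called saliva in 2.8) is for.

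**Cost:** a pipeline flag and targeted assays on a short list, from material already planned for collection. About 5% of true heterozygotes at 30x (1.4% at 60x) would wait for confirmation; they are not discarded. Some ambiguity will remain where blood cells contribute to the swab. Section 2.12 describes recruitment as ongoing, so the rule may still be set before the genetic analysis.

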### Biological filters

2.8

For BAP1, MBD4 and all candidate gene of uveal melanoma, all variants whose frequency in the general population is < 1% will be analyzed. Variants will be classified according to the American College of Medical Genetics (ACMG) recommendations. In addition, if a BAP1 or MBD4 variant is identified in patients who have never had a genetic analysis, the result will be confirmed on the saliva sample and a consultation will be organized to report the results.

For all the others genes, the variants of interest will be selected from the data using the following filters: variants with a frequency <1% (GnomAD), if at least 2 affect the same gene; truncating; splice variant with a SPIP and SpliceAI predicted effect or missense with a combined annotation-dependent depletion (CADD) score > 20 from a list of cancer genes (COSMIC Tier1 and Tier2).

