### In silico analysis

2.9

Each variant of interest will be annotated and interpreted using Alamut Visual (Interactive BioSoftware), which includes splice site analysis tools (MaxEntScan) and protein function prediction tools (SIFT, Polyphen 2.0, REVEL). The variants presenting gene and protein expression in the uveal tissue will be selected, using the protein atlas database (proteinatlas.org). The function of each gene of interest will be interpreted using Genecards (genecards.org), Uniprot (uniprot.org) and Pubmed (https://pubmed.ncbi.nlm.nih.gov/). Proposed splice site variants will also be analyzed using SPIP and spliceAI software. Differential gene expression between tumor and healthy uveal samples will be explored using GEPIA and Expression Atlas databases.

In addition, an enrichment study will be carried out to determine whether the variants identified by the previously applied filters can be linked to the same molecular pathway. Molecular pathways are already defined by online databases (PANTHER, KEGG, *etc.*). The enrichment and associated statistical calculations are carried out on the basis of a list of genes entered into an on-line computer tool (for example https://www.webgestalt.org/, https://biit.cs.ut.ee/gprofiler/gost).

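### The new-gene filter has no class for in-frame insertions and deletions, so those without a predicted splice effect cannot count toward the two-variant rule; the loss of sensitivity is modest

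*Protocol article*

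**What the plan says.** Section 2.8 (Biological filters) of the protocol article sets two regimes.

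- **BAP1, MBD4 and the candidate genes of uveal melanoma:** "all variants whose frequency in the general population is < 1% will be analyzed". Classification by the ACMG recommendations follows. Consequence class is not restricted.
- **Every other gene:** "For all the others genes, the variants of interest will be selected from the data using the following filters". The filters start with "variants with a frequency <1% (GnomAD), if at least 2 affect the same gene" and then admit the classes "truncating; splice variant with a SPIP and SpliceAI predicted effect or missense with a combined annotation-dependent depletion (CADD) score > 20", within the COSMIC Tier 1 and Tier 2 list.

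Section 2.3.1 (Primary objective and outcome measure) gives the selection rule again, with the classes "truncating or missense from a list of cancer genes" and CADD > 20 as a separate item. It has no splice class.

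Upstream, section 2.7 says "Variant calling will be performed using two different tools GATK HaplotypeCaller and FreeBayes", followed by "Variants will be filtered for quality score ≥30, depth ≥ 30x, and present in ≥ 20% of reads". Downstream, section 2.9 interprets the variants of interest, and its enrichment analysis asks "whether the variants identified by the previously applied filters can be linked to the same molecular pathway".

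**The concern.** The primary objective is to nominate new genes, and a new gene is nominated only through variants that pass this filter. An in-frame insertion or deletion adds or removes whole amino acids and leaves the reading frame intact. It is therefore neither truncating nor missense, and unless SPIP and SpliceAI predict a splice effect, it has no way in.

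The loss matters because the rule counts hits and the cohort is small. A gene with two carriers, one of them with an in-frame variant, scores one and is dropped. Among causal variants the error runs only towards missing a true gene. The restriction applies only to the new genes, and the article gives no reason for it.

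The two statements of the rule also disagree with each other: 2.8 admits predicted splice variants and 2.3.1 does not. The class list has to be revisited in any case.

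**Working it through.** **Step 1. Where the class is lost.**

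| Section | What it does | In-frame insertion or deletion |
|---|---|---|
| 2.7 | Filters calls on quality, depth and read fraction | Not removed for its type |
| 2.8, known genes | Analyses all variants below 1% | Kept |
| 2.8, other genes | Truncating, predicted splice, missense with CADD > 20 | Dropped unless it has a predicted splice effect |
| 2.3.1 | Truncating or missense | Dropped |
| 2.9 | Works on variants that passed | Not restored |

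The article does not say in words that in-frame insertions and deletions are called. It follows from the filter itself: the truncating class includes frameshifts, so short insertions and deletions must be in the call set.

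**Step 2. Inputs.** The article gives about 50 patients (2.10) and a threshold of two variants per gene (2.3.1, 2.8). It states no power or detection probability, so there is no figure to reproduce. The rest is assumed:

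- *p*, the share of patients carrying a causal variant in a given true gene: 2% or 4%.
- *s*, the share of those variants that are in-frame and lost at the filter: 2%, 5% or 10%.
- One variant per carrier, carriers independent, and each carrier's variant counted once toward the rule.

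**Step 3. Chance that the gene meets the rule.** With *q* the chance that a patient contributes a qualifying variant,

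P(at least 2) = 1 − (1 − q)^50 − 50q(1 − q)^49.

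If every carrier counts, q = p. If in-frame variants are dropped, q = p(1 − s).

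- p = 2%, all counted: 1 − 0.3642 − 0.3716 = 26.4%.
- p = 4%, all counted: 1 − 0.1299 − 0.2706 = 60.0%.

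| p | All counted | s = 2% | s = 5% | s = 10% |
|---|---|---|---|---|
| 2% | 26.4% | 25.7% (−0.7) | 24.6% (−1.9) | 22.7% (−3.7) |
| 4% | 60.0% | 58.8% (−1.1) | 57.1% (−2.8) | 54.2% (−5.8) |

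Losses, in percentage points, come from unrounded values. At s = 10%, the loss is smaller on either side of this range: 1.5 points at p = 1%, 5.0 at p = 6% and 2.0 at p = 10%.

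**Step 4. Where the loss falls.** A gene with exactly two carriers fails if either variant is in-frame: 1 − (1 − s)² = 4.0%, 9.8% or 19.0% for s = 2%, 5% or 10%. With exactly three carriers it fails only if two or more are in-frame: 3s²(1 − s) + s³ = 0.1%, 0.7% or 2.8%. The problem is largely confined to genes with two carriers.

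**Step 5. Effect of unrelated qualifying variants.** The rule does not ask that a variant be causal. Suppose a share *b* of patients independently carries an unrelated qualifying variant in the gene, so that q becomes 1 − (1 − q)(1 − b). With b = 2% (assumed) and s = 10%:

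- p = 2%: q goes from 3.96% to 3.76%, and the chance from 59.4% to 56.6%. The loss is 2.8 points instead of 3.7.
- p = 4%: q goes from 5.92% to 5.53%, and the chance from 80.4% to 77.1%. The loss is 3.2 points instead of 5.8.

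The losses in step 3 are therefore best read as upper bounds for the assumed s.

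**The case against.** **The filter is deliberate triage.** Reviewing a few high-prior genes widely and a long cancer-gene list tightly is a coherent strategy for exploratory discovery, and each added class brings false nominations as well as true ones. This stands in part. A reader might infer from the known-gene rule that the plan regards in-frame variants as informative and then ignores them. The text does not say that: analysing all variants below 1% carries no judgement on any one class. What remains is that the article restricts the new genes without giving a reason.

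**The class is not wholly shut out.** This is correct. A reader might infer that in-frame variants can never count, but one with a predicted splice effect could enter through the splice class of 2.8. A reader might also take 2.3.1 and 2.8 to impose the same restriction. They do not, since 2.3.1 has no splice class.

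**The list is ambiguous.** If the semicolons separate alternatives, any two rare variants in a gene would pass and nothing would be lost. That reading would also admit truncating variants of any frequency, so the cumulative reading is the natural one.

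**A condensed article may leave class mapping to the full protocol.** It may, but here the rule is stated twice as an operative list, with tools and a cut-off, and as written it leaves this class out.

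**The loss is small and rests on an assumed share.** This stands. The two-variant rule and a cohort of about 50 affect detection far more.

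**Conclusion.** The point holds as a modest gap in the primary-outcome filter. As written, a rare in-frame insertion or deletion without a predicted splice effect cannot count toward nominating a new gene, and no later step restores it.

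For s of 2% to 10% and p of 2% to 4%, the chance that a true gene meets the rule in 50 patients falls by at most about 0.7 to 5.8 percentage points; at s of 5% or less the fall is under 3 points. This rests on an in-frame share and carrier rates that the document does not give, on one variant per carrier, and on independence.

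A reader might take the 4.0% to 19.0% failure rates for two-carrier genes as the overall loss. They are not: they are conditional on exactly two carriers. Nothing here shows that the study's ability to find genes is seriously impaired. The change is worth making because it is cheap and because the two class lists must be reconciled anyway.

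**What to change.** 1. Give one class list in 2.3.1 and 2.8. Settle whether predicted splice variants belong in the primary outcome, and whether CADD > 20 applies to missense only.
2. Add in-frame insertions and deletions with gnomAD frequency < 1% and CADD > 20, within the same COSMIC Tier 1 and Tier 2 list. The article sets that cut-off for missense, so state that it is being extended to this class.
3. Report nominated genes with and without the added class, so that its effect, including any extra false nominations, is visible.

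If the exclusion is intended, say so and give the reason.

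The cost is a line in the filter and in the text, with no new samples or sequencing. The downside is a few additional variants to interpret, most of them probably neutral. The document does not allow their number to be estimated, but the frequency, CADD and gene-list limits hold it down.
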